#### 2.2.3. Sample Calculation

The calculation of the number of participants needed for this study was based on the expected change in quality of life as measured by the EQ-5D-5L questionnaire. Since, to our knowledge, there are no specific data on the minimum clinically relevant change in informal caregivers using this instrument, a minimum difference of 0.07 units was taken as a reference value [39]. Considering a significance level (alpha) of 0.05 and a statistical power greater than 0.8 in a two-sided test, it was determined that 25 participants in the control group and 25 in the experimental group are needed to identify a difference equal to or greater than 0.07 units as significant. A common standard deviation of 0.12 [40] and a correlation coefficient of 0.8 between the initial and final measurements were assumed. In addition, an estimated dropout rate of 25% was calculated. The calculation was performed using version 7.12 of the GRANMO to determine the sample size. (https://www.datarus.eu/aplicaciones/granmo/ (accessed on 10 January 2025)).

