(3)Anxiety and depressionGeneral Health Questionnaire (GHQ-12) [48]. This scale will be used for the assessment of depression and anxiety. It is composed of 12 items (Yes/No). The cut-off point for the anxiety subscale is 4 or more points and 2 or more points for the depression subscale. Higher point values indicate a more severe problem, with 6 being the highest possible value for each subscale. The internal consistency analysis in Spanish population yielded an alpha coefficient of 0.78 [49].Geriatric Depression Scale (GDS). This questionnaire will measure depression and consists of 15 questions about how the participant has been feeling in the last 14 days, with the answers limited to ‘yes’ or ‘no’. The internal consistency analysis yielded an alpha coefficient of 0.87 [50].
(4)Caregiver burdenZarit Burden Inventory (ZBI) (Spanish version). This 22-item questionnaire quantifies caregiver strain. This scale consists of 22 items in a Likert scale format, using a scale from one (never) to five (almost always). The recommended cut-off points are as follows: <46 indicating no caregiver burden; 46 to 56 items indicating mild caregiver burden, and >56 items indicating severe caregiver burden. Its internal consistency is high, with a Cronbach’s alpha coefficient of 0.91 [51].
(5)Occupational balanceOccupational Balance Questionnaire (OBQ-E). This questionnaire assesses participants’ satisfaction with their occupations by the means of 13 items, answered on a Likert scale from zero ‘strongly disagree’ to five ‘strongly agree’. The internal consistency obtained a value of Cronbach’s alpha of 0.948 [52].
(6)Perceived social supportFunctional Social Support Questionnaire DukeUNC-11 [53]. This instrument consists of 11 items that are answered on a Likert scale from 1 to 5, where 1 represents ‘much less than I want’ and 5 ‘as much as I want’, where the questionnaire score ranges from 11 to 55 points. A score of 32 or above indicates standard social support, while a score below 32 suggests low perceived social support. In the Spanish population, the internal consistency of the questionnaire was found to be high, with a consistency coefficient of 0.90 [53].

Assessments will be conducted before the start of the intervention (baseline), at the end of the intervention (8 weeks), and one month after the end of the intervention (12 weeks) (Table 2).

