#### 2.2.7. Statistical Analysis

The data will be analysed with the computer programme IBM Social Sciences (SPSS, version 25.0, Armonk, NY, USA). The normality and homogeneity of the data will be examined by Levene and Kolmogorov–Smirnov tests, respectively. The baseline and socio-demographic characteristics of the study participants will be presented for categorical variables as frequencies and percentages and for continuous variables as means and standard deviations.

The effects of the intervention on the study variables, HRQoL, physical condition, and psychoemotional state (stress, anxiety, depression, caregiver strain, and perceived social support), will be assessed by repeated-measures analysis of variance (ANOVA). The results of the study will incorporate the effect size, together with its corresponding 95% confidence interval, as well as the statistical significance for each measure analysed, considering both the evolution over time and the interaction effects between group and time. If the data do not follow a normal distribution, the Friedman test will be applied. Statistical significance will be established at the conventional level of *p* < 0.05.

In the case of missing data, the Intention-To-Treat (ITT) strategy will be used to maintain the original randomisation and reduce the risk of bias by analysing all participants according to the group to which they were assigned, regardless of their level of adherence.

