
However, it is important to consider some possible limitations to the implementation of the platform. These include the need for financial and technological resources for maintenance and upgrading, as well as training and support for health and education professionals responsible for implementing the programme in real-world settings [62]. In addition, a limitation to consider is the non-probabilistic convenience sampling and the risk of digital exclusion for some caregivers. Some limitations that could affect technological adherence in this group would be low digital literacy, which could lead to insecurity, frustration, and dropout from the programme. Also, the lack of access to devices or internet could limit participation, especially in rural areas or those with a lower socio-economic status. However, given that it is a low-cost healthcare technology that can be easily standardised at different levels of difficulty, its transfer to and implementation in both the public and private sectors could be feasible and sustainable in the long term.

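### Intention-to-treat is given as the answer to missing data, but the named tests use complete cases only, so unless scores are imputed the analysis loses caregivers it promises to include

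*Protocol article*

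**What the plan says.** Three statements in section 2.2.7 of the protocol article bear on this.

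- **Analysis method.** The effects on the study variables "will be assessed by repeated-measures analysis of variance (ANOVA"), with effects over time and group-by-time interactions reported. The fallback is: "If the data do not follow a normal distribution, the Friedman test will be applied".
- **Missing data.** "In the case of missing data, the Intention-To-Treat (ITT) strategy will be used to maintain the original randomisation and reduce the risk of bias", which the sentence goes on to explain as "analysing all participants according to the group to which they were assigned, regardless of their level of adherence".
- **Software.** SPSS version 25.0. No imputation, mixed model or other way of handling a missed visit is named.

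Section 2.2.6 sets the assessments at baseline, "at the end of the intervention (8 weeks), and one month after the end of the intervention (12 weeks"). Section 2.2.3 expects losses: "In addition, an estimated dropout rate of 25% was calculated". Among the limitations, section 3 mentions "low digital literacy, which could lead to insecurity, frustration, and dropout from the programme".

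**The concern.** ITT is a rule about the analysis set: everyone randomised is counted in the arm to which they were assigned, whatever they did afterwards. It does not say what to do when a score was never obtained. The article therefore answers the missing-data question with something that cannot answer it. That differs from leaving the detail to a fuller document.

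The tests named alongside it make this matter. Classical repeated-measures ANOVA over three visits deletes a case if any one of the three scores is absent, and the Friedman test needs complete blocks. A caregiver assessed at baseline and week 8 but not at week 12 is removed from the week-8 comparison as well. Unless missed scores are filled in first, the plan cannot include every randomised participant.

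Two things are at stake. Week-8 scores already collected would be thrown away. And if missing an assessment is related to outcome, completers would be compared with completers and the result reported as ITT.

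**Working it through.** **Inputs.** From section 2.2.3: target difference 0.07 EQ-5D-5L units, SD 0.12, correlation 0.8 between initial and final measurements, two-sided alpha 0.05, power above 0.8, 25 per arm, 25% dropout. From section 2.2.6: three visits. The dropout mechanism and its timing are not in the documents; they are assumed below and marked so.

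**Step 1: reproduce the sample size.**
- SD of change = 0.12 × √(2 × (1 − 0.8)) = 0.0759.
- n per arm = 2 × (0.0759 × (1.960 + 0.842) / 0.07)² = 18.45.
- Allowing for dropout: 18.45 / 0.75 = 24.6, that is 25.

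The stated 25 per arm therefore already contains the 25% allowance. The trial is sized on about 19 completers per arm.

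**Step 2: who would be lost.** 25% of 50 is 12.5, so about 12 randomised caregivers could be missing from a complete-case analysis. About 18.75 per arm remain.

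**Step 3: power with and without them.** For a difference of 0.07 and a change SD of 0.0759:

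| n per arm | Normal approximation | t distribution |
|---|---|---|
| 18.75 (completers) | 0.81 | 0.78 |
| 25 (nobody lost) | 0.90 | 0.89 |

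By the normal approximation, which reproduces the planned n, completer power is still above 0.8. If half of the loss came after week 8 (assumed), keeping those week-8 scores would leave 25 × 0.875 = 21.9 per arm and a t-based power of about 0.85. That is a gain on offer, not the repair of a deficit.

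**Step 4: possible bias at week 8 (illustration, assumed mechanism).** Suppose that loss in the control arm is random. In the experimental arm, suppose that the log-odds of being lost after week 8 rise by 0.5, 1 or 2 for each SD of poorer change from baseline to week 8. Complete-case deletion then shifts the week-8 difference in favour of the intervention. Two timings are shown. In the first, all of the 25% is lost after week 8. In the second, half is lost after week 8, so that 12.5 of the 87.5 per cent seen at week 8, or 14.3%, are deleted.

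| Log-odds slope per SD | All 25% lost after week 8 | Half lost after week 8 |
|---|---|---|
| 0 (random) | 0 | 0 |
| 0.5 | +0.009 (13% of 0.07) | +0.005 (7%) |
| 1 | +0.016 (23%) | +0.010 (14%) |
| 2 | +0.024 (34%) | +0.015 (21%) |
| Limit: all the poorest changers leave | +0.032 (46%) | +0.020 (29%) |

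A separate run with odds ratios of 1.5 to 3 per SD and all of the 25% lost after week 8 gave +0.007 to +0.017 at week 8 and +0.004 to +0.009 at week 12.

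**The case against.** The strongest reply is that the article never says incomplete cases will be excluded. It says the reverse, and repeated-measures ANOVA on imputed scores would satisfy both sentences. The article is a condensed account, and the imputation technique is commonly left to an analysis plan. This stands in part. Imputation would reconcile the text, so a completer analysis follows only if nothing is imputed. But the article does not leave the question open: it names a missing-data strategy that cannot do the job, beside tests that need complete data.

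A reader might also infer that loss will be confined to the experimental arm, and so be differential, because section 3 links low digital literacy to dropout. The documents do not support this. That sentence concerns leaving the programme, whereas the outcomes come from a questionnaire booklet scheduled for both groups at all three visits (section 2.2.6 and Table 2). Someone who stops using the platform can still fill in the booklet. Control caregivers, who know their allocation and receive no programme, may leave too, which could offset or reverse any bias. The weekly calls in section 2.2.5 may also limit losses in the experimental group. Differential, outcome-related loss is possible but not established.

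A further tempting reading is that the trial becomes underpowered. Step 1 rules that out, since the planned number already allows for the loss.

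**Conclusion.** The point holds in limited form. As written, the missing-data rule and the named tests cannot together deliver an analysis of every randomised caregiver unless missed scores are imputed, and no imputation is mentioned. On the protocol's own allowance, about 12 of 50 caregivers could be excluded from an analysis labelled ITT, with their observed week-8 scores discarded where they exist.

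The sample size is not in error. The size of any bias is hypothetical: zero under random loss, and about +0.005 to +0.024 EQ-5D units at week 8 if loss in one arm depends on week-8 change with a log-odds slope of 0.5 to 2 per SD and half or all of the 25% falls after week 8. The slopes, the timing and the restriction to one arm are assumptions, and 25% is itself a planning figure. The plan should be corrected before analysis, because the same method serves the HRQoL and psychoemotional outcomes alike, but the documents do not show that the result will be biased.

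**What to change.** 1. Keep ITT as the definition of the analysis set only.
2. Name a method that uses incomplete cases. The simplest is a likelihood-based linear mixed model for repeated measures, with group-by-visit terms and baseline adjustment, using every available score from every randomised caregiver; SPSS fits it with its MIXED procedure. Multiple imputation followed by the planned ANOVA would also close the gap.
3. State that questionnaires are still collected at weeks 8 and 12 from caregivers who stop using the platform.
4. Add one sensitivity analysis for data not missing at random, for example a delta-adjusted imputation. It is needed because the mixed model does not remove bias from early loss for unobserved reasons.

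The cost is a change of wording, a different SPSS procedure and slightly more analysis work, with no extra visits or participants. The main analysis would then rest on a missing-at-random assumption, which should be stated.

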## 3. Discussion

This research protocol is innovative in its approach to physical activity and health promotion for informal caregivers of people with dementia. The expected findings will show how physical activity, access to training courses, and psychoemotional and social support have a positive impact on the quality of life (HRQoL) and psychoemotional health of informal caregivers [2].

Firstly, it has been identified that the global increase in life expectancy and the prevalence of dementia generate an increase in the demand for care [3]. This situation translates into increased strain on caregivers, mostly elderly women, who experience physical and emotional overload [9,10]. Health literacy is, therefore, of particular relevance, since, as pointed out by Liu, Wang, Liu, Jiang, Wang, Chen, Ju, and Zhang [15], this enables carers to obtain, process, and apply information to maintain and improve their health in a way that is tailored to their particular context.

Currently, the literature shows insufficient health literacy among caregivers [17], a fact that influences both the quality of care provided and the caregiver’s well-being [18]. In particular, it has been observed that caregivers with low health literacy may have higher levels of caregiver strain, a lower quality of life, and even spend more time on caregiving due to a lack of effective coping strategies [19]. In this sense, the CAREFIT programme addresses this knowledge gap by offering, through the platform, training and support resources to promote self-care.

The benefits of physical activity in the adult population improve both physical fitness and mental health [20,21]. The case of informal caregivers of people with dementia is of particular importance, given that many of them start with a poor physical condition [20]. According to da Silva-Sauer, Garcia, Fonsêca, and Fernández-Calvo [22], the restriction of physical activity is associated with increased somatic complaints and an increased caregiving burden. Farina, Williams, Clarke, Hughes, Thomas, Lowry, and Banerjee [23] emphasise the importance that caregivers attach to physical activity for their own emotional and social well-being. Under this premise, the inclusion of adapted exercise and active living patterns in CAREFIT has the potential to improve cardiovascular health and general fitness, as well as being a protective factor against stress and depression [24,25,26].

Given the multicomponent nature of the CAREFIT intervention programme, focusing on physical activity, resilience, and psychoemotional well-being, it is anticipated that its effectiveness could vary according to the specific socio-demographic characteristics of participating caregivers, such as age, gender, and educational level.

In this sense, younger caregivers may show a greater capacity for physical adaptation to the active components of the programme, which would favour significant improvements in their general physical state and, therefore, in their perception of health-related quality of life (HRQoL). However, older caregivers may benefit more from the emotional and social component, as they tend to experience a greater degree of isolation and sustained emotional burden. In these cases, a focus on resilience and perceived social support may be particularly effective in mitigating symptoms of anxiety, depression, and caregiver burden [54]. On the other hand, studies indicate that women are more likely to assume the role of primary caregivers and, as a result, report higher levels of stress and strain. In this sense, the programme is expected to have a particularly positive impact on female caregivers by providing them with coping tools and opportunities for self-care [55]. In contrast, male caregivers, although less represented in this role, may experience benefits in terms of emotional connection and stress management, aspects that are often less developed in this group due to traditional social norms [56]. Finally, level of education may influence understanding and adherence to the programme. Caregivers with a higher level of education may show a better assimilation of the psychoeducational contents and a greater willingness to implement the proposed changes in their daily routine [57]. However, less educated carers are not exempt from the benefits; for this group, accessibility of language, clarity of instructions, and close accompaniment will be key factors in encouraging active and sustained participation [58].

In this sense, the adoption of digital resources not only facilitates the accessibility of information, but also enables personalisation and the continuous monitoring of adherence to the programme, overcoming geographical or logistical barriers [27,28]. In addition, the integration of psychoeducational and emotional support content, such as in the work of Cristancho-Lacroix, Wrobel, Cantegreil-Kallen, Dub, Rouquette, and Rigaud [28], offers a closer accompaniment to the caregiver, favouring the reduction in caregiver burden and the improvement of self-confidence in the management of care situations.

Furthermore, the multidisciplinary approach, encompassing educational support, physical activity, psychoemotional support, and social support, is in line with evidence indicating that interventions in multiple areas tend to report better outcomes in terms of adherence and effectiveness [29,32]. For example, Lamotte, Shah, Lazarov, and Corcos [32] evidence that physical exercise programmes, coupled with an educational component, improve quality of life and reduce caregiver burden. This comprehensive approach can be instrumental in promoting sustainable changes in caregivers’ lifestyles and maintenance of their own health. This is why the present protocol can bring health literacy benefits, improved quality of life, improved physical condition, and emotional support using a technological application, which can be adapted to each caregivers’ rhythm of life. In this sense, it has been observed that on-demand interventions, where the caregiver can perform activities without a set frequency, have had better results [59]. In short, the use of technological solutions has proven to be an effective solution to reduce caregiver burden, improve quality of life, and avoid the negative physical and psychological consequences of caring for a dependent person [60,61]. However, in order to maintain the long-term effects of the CAREFIT programme on caregivers of people with dementia, it is essential to incorporate follow-up, reinforcement, and sustainability strategies that ensure the integration of the learned habits into daily life. Finally, regarding the strengths of the study, this study could play a key role in reducing the social isolation of carers, promoting their social inclusion and the creation of support networks. Ultimately, the CAREFIT platform is designed to respond to the specific needs of carers, offering tailored and relevant resources that can make a significant difference in their daily lives. Facilitating active ageing and improving the quality of care provided are central objectives of this initiative. In addition, one of the greatest strengths is the importance of the transferability of the results of this project. If the intervention proves effective, its applicability could be extended not only to caregivers of people with dementia, but also to other informal care settings for chronically ill patients. Furthermore, the incorporation of the platform into public health services or institutional programmes could facilitate a standardised and low-cost intervention, with positive repercussions in reducing the high social and healthcare costs derived from the overburden of caregivers [6,10]. This would favour the implementation of more efficient support policies, aimed at both the promotion of the carer’s health and the improvement of the care provided to the patient.

However, it is important to consider some possible limitations to the implementation of the platform. These include the need for financial and technological resources for maintenance and upgrading, as well as training and support for health and education professionals responsible for implementing the programme in real-world settings [62]. In addition, a limitation to consider is the non-probabilistic convenience sampling and the risk of digital exclusion for some caregivers. Some limitations that could affect technological adherence in this group would be low digital literacy, which could lead to insecurity, frustration, and dropout from the programme. Also, the lack of access to devices or internet could limit participation, especially in rural areas or those with a lower socio-economic status. However, given that it is a low-cost healthcare technology that can be easily standardised at different levels of difficulty, its transfer to and implementation in both the public and private sectors could be feasible and sustainable in the long term.

## 4. Conclusions

The proposed protocol for the CAREFIT programme, based on a digital platform, offers an innovative and multidisciplinary approach using technology to improve the quality of life of informal caregivers of people with dementia. By integrating health and physical activity literacy with psychoemotional and social support, it is expected to reduce overload, stress, anxiety, and depression in informal primary caregivers, as well as strengthen their support networks and self-care skills.

Given that the planned technology-assisted interventions meet the requirements of flexibility and accessibility, it will facilitate the acquisition of healthy lifestyle habits and favour an improvement in mental health. If the programme proves to be effective, its results could be applied more widely in the social health field, being incorporated into public or private care policies and plans, in order to support the well-being of both caregivers and dementia patients themselves.

